#### Allocation concealment mechanism {22}

Participant enrolment will be performed by the research team, who will conduct screening, data collection and study explanations. After consent, the clinical assessment will be performed, including HADS administration.

#### Implementation {23}

Assignment to interventions will be carried out by an external biostatistician using a pre-generated randomization sequence, ensuring impartial and concealed allocation to control or VR intervention groups. Randomization will occur after informed consent is obtained and baseline assessments are completed, preventing selection bias. The biostatistician responsible for randomization sequence generation, concealment and allocation has no direct contact with study participants, no involvement in participant recruitment or eligibility screening, no role in intervention delivery or supervision and no access to outcome data during trial conduct. This individual’s sole responsibility is generating the randomization sequence using appropriate methodology (block randomization with 1:1 allocation ratio), maintaining allocation concealment via secure electronic system and revealing allocation assignments only after participant informed consent and baseline assessment completion.

All randomization activities are conducted remotely via secure electronic communication (REDCap platform with restricted access). Participants and trial staff will not be able to predict or influence allocation assignments, as the randomization sequence is generated remotely and revealed only at the designated time. Physical separation of randomization personnel from clinical trial conduct ensures complete independence and minimizes risk of selection bias or allocation manipulation. The external biostatistician will maintain the randomization sequence in a secure.

### Assignment of interventions: blinding

#### Who will be blinded {24a}

##### Blinding limitations

Due to the nature of the VR intervention, participants and the physiotherapist cannot be blinded. Participants will necessarily be aware of whether they are receiving standard exercise or VR-augmented exercise, as the presence or absence of the immersive VR headset is inherently visible. Similarly, the physiotherapist delivering the intervention must know group allocation to deliver the assigned intervention appropriately.

##### Measures to minimize bias

Despite the lack of participant and intervention provider blinding, bias will be minimized through the following strategies:Objective measurement standardization: Vital signs and exercise duration will be recorded using calibrated, automated monitoring equipment in real-time, reducing observer bias in physiological measurements.Standardized procedures: All participants in both groups will receive identical exercise protocols, duration, intensity monitoring procedures and standardized verbal instructions, ensuring that measurement procedures are equivalent across groups.Data analyst blinding: Statistical analyses will be conducted by an external biostatistician using blinded data coding (Group A/Group B only), without knowledge of intervention group assignment during analysis to prevent analysis bias.Allocation concealment: Participants and clinical staff will not know group assignment until after baseline assessments are completed.

### How will be blinding be achieved {24b}

Data analyst: Blinded to group allocation during statistical analysisExternal randomization manager: Maintains allocation concealment until baseline assessments are completeParticipants and physiotherapist: Cannot be blinded due to intervention visibility, but will not be informed of trial hypotheses or expected outcomes

The data analyst will remain blinded to group allocation until completion of all primary statistical analyses and generation of the primary results table. Group identities will be revealed to the analyst only after the primary analyses have been completed, documented and verified.

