### Trial design {12}

This study is a randomized, controlled, parallel-group clinical trial. Participants will be randomly allocated in a 1:1 ratio to either the control or immersive VR intervention group. Allocation will be conducted by an external researcher uninvolved in recruitment or intervention delivery, and data analysts will be blinded to group assignments. The trial investigates the effects of immersive VR on exercise tolerance in hospitalized heart failure patients, aiming to generate foundational evidence to support the use of immersive technologies in cardiac rehabilitation.

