### Statistical methods

#### Statistical methods for primary and secondary outcomes {27a}

Analyses will be performed using SPSS Statistics v25.0 with significance level α = 0.05 (two-tailed). Primary outcome (total exercise duration) will be compared between groups using independent-samples *t* test, or Mann–Whitney *U* test if normality is violated (Shapiro–Wilk *p* < 0.05). Secondary outcomes will be compared using appropriate parametric or non-parametric tests. Likert-scale items will be analyzed using Mann–Whitney *U* tests. Descriptive statistics (means ± SD, medians [IQR]) will characterize all outcomes.

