#### How missing data will be handled in the analysis {27c}

For primary and secondary outcomes, every effort will be made to minimize missing data through robust follow-up and documentation procedures during the single-session design. If missing data occur for the primary outcome, a complete-case analysis will be performed. As a sensitivity analysis, multiple imputation will be considered if the proportion of missing data exceeds 5%. Missing data patterns and reasons will be described in detail. All analyses involving missing data will be clearly reported, and no participants will be excluded solely due to missing data for secondary or exploratory outcomes.

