#### Methods for additional analyses (e.g. subgroup analyses) {27d}

Pre-specified subgroup analyses will examine potential treatment effect modifications by age, sex, LVEF and NYHA functional class. Subgroup-by-treatment interactions will be tested using linear regression with group-by-variable interaction terms. The significance threshold for interactions is α = 0.10 (exploratory). Results should be interpreted cautiously given potential for Type I error. Multivariable linear regression models will be used to adjust outcomes and control for potential confounders in secondary analyses.

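### The analyst's blind is described as covering the statistical analyses, but the release rule ends it once the primary results table is done

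*Protocol article*

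**What the plan says.** Three statements give the analyst's blind no end. Trial design {12} says that "data analysts will be blinded to group assignments". Measures to minimize bias says that an external biostatistician will work on data labelled only as Group A and Group B, "without knowledge of intervention group assignment during analysis to prevent analysis bias". The first bullet of {24b} likewise says the analyst is blinded during the statistical analysis.

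The closing paragraph of {24b} then sets the end point: "The data analyst will remain blinded to group allocation until completion of all primary statistical analyses and generation of the primary results table". It repeats the condition: "Group identities will be revealed to the analyst only after the primary analyses have been completed, documented and verified".

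The analyses themselves are set out in {27a} to {27d}. The primary test is a t test, or Mann–Whitney if Shapiro–Wilk gives p < 0.05. For the rest:

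- {27a}: "Secondary outcomes will be compared using appropriate parametric or non-parametric tests".
- {27b}: a per-protocol analysis, labelled secondary, is compared with the intention-to-treat result.
- {27c}: as a sensitivity analysis, "multiple imputation will be considered if the proportion of missing data exceeds 5" per cent.
- {27d}: "Pre-specified subgroup analyses will examine potential treatment effect modifications by age, sex, LVEF and NYHA functional class", and "Multivariable linear regression models will be used to adjust outcomes and control for potential confounders in secondary analyses".

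**The concern.** Two parts of the protocol give different scopes for the same safeguard. A reader of the bias section would take it that whoever compares enjoyment, heart rate or perceived exertion between groups does not know which group wore the headset. A reader of the release rule would learn that this is assured only for the primary analyses.

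Analyst blinding carries more weight here than in many trials. The section on blinding limitations says that neither participants nor the physiotherapist can be blinded, so it is one of the few protections left. Enjoyment (PACES), the first secondary objective listed, is self-reported by patients who know their arm. Future directions and expected outcomes states that longer exercise and higher enjoyment are expected with VR. An analyst who knows the arms and the expected direction could, without intending to, probe an unwelcome secondary result further than a welcome one.

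**Working it through.** There is no figure in the plan to reproduce. The check is to take each between-group analysis and ask whether the release rule in {24b} keeps the analyst blinded for it, and how much judgement the article leaves open.

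| Analysis | Section | Blind assured by the release rule? | Left open in the article |
|---|---|---|---|
| Primary, exercise duration, ITT | {27a}, {27b} | Yes | Almost nothing: the test follows a fixed rule |
| Secondary outcomes | {27a} | No | Choice of test, except that Likert-scale items are assigned to Mann–Whitney |
| Per-protocol | {27b} | No | Little: the population is defined as those completing the session |
| Imputation sensitivity analysis of the primary outcome | {27c} | Not stated | Whether to impute above 5% missing, and the model |
| Adjusted regression | {27d} | No | Which covariates |
| Subgroup interactions | {27d} | No | Little: four factors, linear regression with interaction terms and a 0.10 threshold are fixed; the coding of age, LVEF and NYHA class is not |

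Three things follow.

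1. The conflict of scope is on the page. Three statements give the blind no limit, and the release rule ends it at the primary results table. Nothing in the document extends it to the later analyses.

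2. As far as the article goes, the blind is assured for the step with least discretion. The steps with most discretion (secondary tests, imputation, covariates) are those for which it is not assured.

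3. The rule sets an earliest time for release. It neither requires the later analyses to wait nor says that they will be run unblinded. The correct strength is that they may be.

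**The case against.** **The word primary could be read widely.** The release rule speaks of primary analyses in the plural, and {27b} uses primary for the intention-to-treat analysis as a whole. On that reading the blind might already cover the intention-to-treat comparisons of secondary outcomes, and the imputation analysis of the primary outcome might count as primary too. The latter is possible, though not stated. The former is strained: {27a} to {27d} separate primary outcome from secondary outcomes and place the per-protocol and adjusted analyses under the secondary label. If the wide reading is intended, the text should say so.

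**The open choices may be closed elsewhere.** A protocol article commonly leaves tests, imputation models and covariates to the analysis plan, which may exist but is not shown. This stands. Their absence is not the point made here. A plan that fixed them would shrink the consequence, but the release rule would still be narrower than the safeguard claimed.

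**A reader might infer a measurable rise in false-positive results from early unblinding.** The documents do not support one. A simulation with no true effect, 30 per arm and 4,000 trials per setting let the analyst choose among the t test, Mann–Whitney and 15 covariate-adjusted models. The four covariates, each explaining 0, 5 or 10% of variance, are assumptions that the protocol does not supply. An analyst who knew the arms and picked in favour of VR obtained a false result favouring VR in 3.7%, 5.0% and 6.8% of trials. An analyst still blinded to A/B who reported the smallest p-value obtained the same 3.7%, 5.0% and 6.8%. The candidate analyses are so closely correlated that they hardly ever reach significance in opposite directions. The excess over the nominal 2.5% in one direction therefore comes from free choice of model, and longer blinding would not remove it. Knowing the arm adds something only where results against VR are selectively played down, and that has not been quantified.

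**A reader might also infer that the subgroup analyses are wide open.** They are not: factors, model and threshold are stated, and the results are labelled exploratory.

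**Conclusion.** The point holds as an inconsistency with a small practical consequence. The analyst's blind is presented as a safeguard for the statistical analyses, but the release rule assures it only up to the primary results table. The secondary-outcome, per-protocol, sensitivity and adjusted comparisons may be run with the arms known.

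The primary comparison is protected under every reading, so the main conclusion of the trial is not threatened. No numerical size is attached, because none can be derived from the documents. The remaining risk is uneven handling of results that go against the expected direction. That risk is largest if the choices left open in {27a}, {27c} and {27d} are still open at analysis, and much smaller if an analysis plan fixes them beforehand. The verdict assumes that primary carries the meaning it has in {27a} to {27d}.

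**What to change.** Amend the closing paragraph of {24b} so that group identities are revealed only after all planned between-group analyses under {27a} to {27d} (primary, secondary, per-protocol, missing-data, adjusted and subgroup) have been run under A/B coding, documented and archived. Use the same description of scope in Measures to minimize bias, so that the two sections agree.

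The new sentence needs one practical provision. SUS is collected in the VR group only, and headset-specific events can occur only there, so either would break an A/B code once it is in the analysis file. Hold these data back and analyse them last.

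The cost is one or two sentences and a fixed order of analysis, with no additional patients, data or staff. Recruitment is expected to run to 10 November 2026, so the change can go through the procedure in Protocol amendments {31} before recruitment ends.

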### Procedure for unblinding if needed {24c}

If it becomes necessary to reveal a participant’s allocation, unblinding will occur in a controlled manner. The person responsible for randomization and case oversight may access the participant’s assignment through a secure system without sharing that information with other team members or influencing outcome assessments. All unblinding decisions will be documented with justification and context.

### Data collection and management

#### Plans for assessment and collection of outcomes {25a}

Data will be collected by trained physiotherapist who will supervise all exercise sessions and record data using standardized case report forms (CRF). Patient-reported satisfaction with the exercise experience will be assessed using the Physical Activity Enjoyment Scale (PACES) [18, 19], a 18-item self-report questionnaire administered immediately post-exercise to both groups. For the VR intervention group, system usability will be assessed using the System Usability Scale (SUS) [20, 21], a 10-item questionnaire administered immediately post-exercise to measure ease of use, comfort and perceived immersion with the VR technology.

Vital signs monitoring will be performed before, during (every minute) and after exercise using standardized equipment: pulse oximetry for oxygen saturation (SpO₂), automated sphygmomanometer for systolic and diastolic blood pressure (BP) and continuous heart rate monitoring via pulse oximeter and ECG. Continuous 12-lead ECG monitoring via bedside cardiac monitor will be performed during all exercise sessions for safety surveillance. Continuous ECG waveforms during the exercise session will not be archived. Only ECG strips corresponding to detected clinically significant arrhythmias (atrial fibrillation, ≥ 6 consecutive ventricular ectopic beats, sustained ventricular tachycardia** > **3 beats) or ischemic changes (≥ 1 mm ST-segment deviation from baseline) will be saved for post-hoc review by a blinded cardiologist.

Perceived exertion will be assessed using the Modified Borg Rating of Perceived Exertion Scale (0–10), administered at baseline, every minute during exercise and post-exercise to monitor exercise intensity and participant tolerance. All outcome data will be recorded in real-time on standardized forms during the exercise session to minimize measurement error and recall bias. Post-exercise questionnaires (PACES and SUS) will be administered while participant experience remains fresh, typically 5–10 min after exercise completion. All data will be entered into the secure REDCap database with mandatory quality checks for completeness, consistency and integrity before database lock.

#### Plans to promote participant retention and complete follow-up {25b}

Continuous monitoring: During hospitalization, patients will be supported by a multidisciplinary team (physician, nutritionist, pharmacist, psychologist, physiotherapist and nurse).Active engagement: Before starting, participants will be informed about the benefits of the intervention; VR will be presented as an innovative tool to enhance the experience.Personalized support: The team will offer ongoing assistance and address questions; participants may interrupt or modify the intervention if needed without jeopardizing care.Detailed records: All deviations/interruptions will be recorded; participants who withdraw will be followed to document reasons and mitigate impact.Clear communication: From admission to discharge, the study’s importance and participants’ contribution will be emphasized.

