### Who will take informed consent? {32a}

Informed consent will be obtained by trained members of the research team, specifically the Principal Investigator ([name] [name]) or designated research coordinators trained in Good Clinical Practice (GCP) and the study protocol.

The informed consent form will detail all relevant study information, including: trial objectives, procedures, expected duration of participant involvement, potential risks and benefits, confidentiality protections and voluntary nature of participation. The form will be provided to participants (or their legal representatives if applicable) in Portuguese, allowing sufficient time for review and questions before written consent is obtained.

Participants will have the opportunity to ask questions and discuss any concerns with the research team before deciding whether to participate. Participation is entirely voluntary, and participants may withdraw at any time without affecting their standard clinical care or treatment at the institution.

All informed consent procedures will be conducted and overseen by the Research Ethics Committee of UNIFESP to ensure compliance with Brazilian regulations (CONEP—National Research Ethics Commission), the Declaration of Helsinki and International Council for Harmonisation (ICH) guidelines for research involving human participants.

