### Strategies to improve adherence to intervention/comparator {15c}

Adherence is promoted through comprehensive participant engagement: detailed informed consent integrated into routine clinical care with emphasis on study contribution to cardiac rehabilitation science and minimal burden (single session). During exercise, continuous physiotherapist supervision provides real-time guidance, encouragement and safety oversight. The VR group benefits from a structured 5-min familiarization process minimizing technology anxiety, an immersive scenic virtual environment with synchronized avatar movement providing biofeedback.

Post-exercise, participants receive immediate feedback on total exercise time, positive reinforcement and PACES/SUS questionnaires administered while experience is fresh. Study purpose is communicated emphasizing potential benefit to future heart failure patients. For this single-session design, adherence encompasses participant attendance and protocol completion while maintaining safety, comfort and sense of agency.

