## Future directions and expected outcomes

Our pilot study [17] demonstrated feasibility of immersive VR exercise in hospitalized HF patients. This REVIVE-HF trial represents a rigorous advancement with adequate sample size, randomized design and predefined outcomes. We expect the VR group to achieve longer exercise duration and higher enjoyment (PACES) and usability (SUS) scores compared to controls. If confirmed, this protocol could be adapted to other hospital contexts and incorporated as a complementary resource in cardiac rehabilitation programs, contributing to innovation in acute care.

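### Participants are to hear VR presented favourably before the session, although the blinding section promises to keep the trial's expectations from them

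*Protocol article*

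**What the plan says.** The protocol article accepts that neither participants nor the physiotherapist can be blinded. Section {24b}, on how blinding is achieved, limits what they are told: "Cannot be blinded due to intervention visibility, but will not be informed of trial hypotheses or expected outcomes".

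Section {25b}, on retention and complete follow-up, says what participants will hear ahead of the session: "Before starting, participants will be informed about the benefits of the intervention; VR will be presented as an innovative tool to enhance the experience". The sentence speaks of participants generally and is not restricted to one arm.

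The trial's expectation is set out under Future directions and expected outcomes: "We expect the VR group to achieve longer exercise duration and higher enjoyment (PACES) and usability (SUS) scores compared to controls". SUS is collected in the VR arm only, so the outcomes that can be compared between arms here are exercise time and PACES.

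Two further places govern what participants learn. Section {32a} on consent says: "The informed consent form will detail all relevant study information, including: trial objectives, procedures". Section {15c} on adherence says: "Study purpose is communicated emphasizing potential benefit to future heart failure patients".

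On what follows the session, {15c} says: "Post-exercise, participants receive immediate feedback on total exercise time, positive reinforcement and PACES/SUS questionnaires administered while experience is fresh". Section {25a} gives the timing: "Post-exercise questionnaires (PACES and SUS) will be administered while participant experience remains fresh, typically 5–10 min after exercise completion". The same section also describes both questionnaires as given immediately after exercise.

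**The concern.** In an open-label trial, withholding the expected direction is one of the few ways to limit what participants bring to a subjective rating. Section {24b} claims that protection, and {25b} removes it by telling participants that one of the two conditions improves the experience. PACES then asks them how much they enjoyed the experience.

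At stake is the interpretation of a difference favouring VR. The last part of {15a} says that any difference can validly be attributed to VR itself. If participants have been told beforehand that VR improves the session, an effect of that suggestion cannot be separated from an effect of the technology. Controls who hear the same message know that they are exercising without the tool, which could lower their ratings and so act in the same direction.

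**Working it through.** No figure in the protocol bears on this point, so the check sets the sections side by side.

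1. **Can {24b} and {25b} both be followed?** {24b} rules out telling participants the hypotheses or the expected results. {25b} has them told of benefits and has VR described as improving the experience. The expected results include higher enjoyment with VR. Telling someone that VR improves the experience conveys that expectation in substance. The two instructions conflict.

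2. **Does another reading of {25b} remove the conflict?** The first clause, on benefits of the intervention, could mean the benefits of exercise. The second clause names VR, so the conflict remains.

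3. **Do consent and study purpose conflict with {24b} as well?** Not necessarily. Stating an objective tells participants the question; it need not tell them the expected answer. {32a} and the study-purpose sentence in {15c} are compatible with {24b} if their wording does not say which arm should do better. If it does, deleting the {25b} sentence alone would not restore {24b}.

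4. **Which outcomes are open to expectancy?**
   - PACES: fully self-reported, given to both arms after the session. Most exposed.
   - Exercise time: under {15b} the session ends if the participant asks to stop for any reason, or rates dyspnea or leg fatigue at 5 or more on the modified Borg scale. Those routes depend on the participant's judgement. The same section also ends the session on blood pressure, heart rate, ECG changes, clinical signs or failure of the monitoring systems, which are less open or not open to expectancy. The session is also capped at five 3-minute blocks, so a participant who completes them has no further time to gain. Exposure is partial.

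5. **Do the other bias measures cover this?** {24a} lists objective measurement, standardized procedures and instructions, analyst blinding and allocation concealment. Automated recording protects the measurement of time, and a blinded analyst protects the analysis. Concealment protects the assignment. Standardized delivery makes a favourable message uniform without making it neutral. None acts on what the participant expects once the session begins.

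6. **Where does PACES fall relative to feedback?** {15c} lists immediate feedback on time and positive reinforcement ahead of the questionnaires. {25a} places the questionnaires typically 5 to 10 minutes after exercise but also says immediately afterwards. The listing suggests that feedback comes first, but no section fixes the order.

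**The case against.** The strongest reply is that an open-label trial with informed consent cannot keep participants ignorant of what is compared, and that controls will always know they have no headset. That stands. It concerns knowledge of the allocation and the question, however, and the sentence in {25b} goes further by supplying the favoured answer.

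It can also be said that the message concerns the experience and not how long to pedal, and that many stops are physiological or technical. This stands too, and is why the point rests chiefly on PACES and only plausibly on the primary endpoint. Likewise, withholding hypotheses is not among the four measures listed in {24a}, so it should not be described as the trial's only protection.

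Three stronger readings are tempting but unsupported:

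- A reader might infer that praise and feedback before PACES push the result toward VR. The order is not fixed, and {15a} makes post-exercise handling identical in both arms, so feedback is not differential in itself. It would become so only if times differed by arm or unblinded staff praised unequally, and the protocol states neither. Controls can also see their time on the ergometer display.
- A reader might infer that encouragement during pedalling is unstandardized. {15c} mentions encouragement without describing its form, {24a} promises standardized verbal instructions, and an article may leave exact wording to fuller procedures.
- A reader might want the bias expressed as a share of the planned effect. The document gives no size for an expectancy shift, so any such figure would only restate an assumption.

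**Conclusion.** The conflict between {24b} and {25b} is certain on the text and needs correction. The consequence is a reasoned risk, not a demonstrated bias: expectancy favouring VR, mainly in PACES and plausibly in that part of exercise time which participants themselves end. Its size is unknown. The direction rests on two assumptions: that participants take the message as favourable to VR, and that self-ratings and decisions to stop respond to it. The order of feedback and PACES is a secondary matter that needs clarifying and is not an established source of bias between arms.

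**What to change.** 1. In {25b}, replace the sentence on benefits and on the presentation of VR with one neutral script used in both arms, for example: *the study compares two ways of doing the same exercise, and it is not known whether they differ*.
2. Keep the consent wording ({32a}) and the study-purpose wording ({15c}) neutral on which arm is expected to do better. Objectives, risks and potential benefits can still be disclosed as consent requires, and {24b} then holds as written.
3. As a secondary safeguard, state in {15c} and {25a} that PACES, then SUS in the VR arm, is completed before any feedback on exercise time or positive reinforcement.

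The sample size, the data collected and the analysis are unchanged. What is lost is a retention message, which matters little when each participant attends one session. Recruitment was due to start on 10 November 2025 and to run to 10 November 2026, so the change would go through the amendment procedure in {31}. Its effective date should be recorded so that participants who received the earlier message can be identified.
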